#### Objective 4: Machine Learning

Although group-based statistical analysis is useful for drawing conclusions about general trends, it has limited utility for guiding individual diagnostic and treatment choices.

As a result, in addition to conventional statistical analysis, this study will explore the application of machine learning in an attempt to identify individual data patterns that may predict diagnosis, severity, and potential treatment outcomes. Physiological, biometric, biological, and qualitative data from T0 to T3 will be used to predict psychological outcome measures at week 9 plus follow-up sessions. A model that can compute sequential, multimodal data is needed to autonomously observe and learn the variability of the relevant feature sets and its association with outcome measures [57,58]. Deep neural networks will be applied for this task [57,58].

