### Hypotheses

Related to the objectives above, we have derived the following four hypotheses for this study.

Hypothesis 1: Participants’ symptoms of combat-related TR-PTSD will decrease during the 3DMR therapy compared with treatment as usual.

Hypothesis 2: CAF-SMs, veterans, 3MDR clinicians, and operators will perceive 3MDR to be a novel intervention with adequate perceived technology acceptance and usability.

Hypothesis 3: 3MDR operators and clinicians will not experience adverse mental health effects, including secondary trauma and stress, that affect their daily functioning as a result of 3MDR delivery.

Hypothesis 4: Machine-learning analysis will generate two accurate predictive models that may portend diagnosis, severity, and potential treatment outcomes in CAF-SMs and veterans with combat-related TR-PTSD.

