### Recruitment

Regular and reserve CAF-SMs and veterans will be recruited through established relationships with the CAF, Operational Stress Injury Clinics, the Royal Canadian Legion Alberta/Northwest Territories Command, and local community service providers supporting CAF-SMs and veterans. Participants will also be recruited through word of mouth among potential participants. Eligible participants include English-speaking regular and reserve CAF-SMs and veterans aged 18-60 years who meet the Diagnostic and Statistical Manual-5 (DSM-5) criteria for a diagnosis of PTSD. This includes: (1) symptoms lasting more than 3 months; (2) a score of 30 or higher on the DSM-5 Clinician-Administered PTSD Scale, Fifth Edition (CAPS-5) interview; (3) trauma related to combat experiences; and (4) have had a nonresponse to at least two types of evidence-based PTSD treatments where at least one of these treatments was a psychotherapeutic intervention. It is permitted that the second treatment is a pharmacological intervention. Participants must also be stable on their psychotropic medication for a period of 4 weeks before entering the trial and agree to notify researchers of medication adjustments during the course of the trial. Participants with comorbidities will be included if they satisfy the other criteria and PTSD is considered the primary diagnosis. Participants must also have the cognitive capacity to provide informed consent. Participants will be excluded from the study if they demonstrate signs of acute suicidality, psychosis, or reduced cognitive processing that would exclude them from following directions or providing informed consent. Participants will also be excluded if it is determined that they are unable to walk at a normal pace for 30-45 minutes on a treadmill, or if their physical size or abilities are not compatible with the CAREN system. For CAF-SMs and veterans, screening by a research team member will consist of an interview to discuss their previous military employment/deployments, current and past medical history, history and experiences of previous PTSD interventions, and overall suitability for the study.

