### Study Timeline and Data Collection

#### Objective 1: Effectiveness of 3MDR

Data will be collected from intervention and control group participants at initial assessment (T0), prior to delivery of 3MDR (T1), pre/post 3MDR sessions (T2.1-2.6), and at 1 week (T3), 1 month (T4), 3 months (T5), and 6 months (T6) postintervention (Figure 3).

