**Figure 3 figure3:**
[figure not shown]
Multimodular motion-assisted memory desensitization and reconsolidation (3MDR) data collection time points for the intervention (treatment; blue/red) and waitlist control (green) groups. The syringe icon denotes blood collection and the square icon denotes saliva collection.

Clinical outcome measures will be collected at each time point using the questionnaires listed in Table 1. Qualitative interviews will occur at T3 through T6. Physiological, biometric, and qualitative audio/video data will be collected at T2.1-T2.6. Blood and saliva samples will be collected at baseline (T1), before (pre) and immediately after (post) 3MDR sessions at T2.1 and T2.6, post 3MDR sessions at T2.3 and T2.4, at 1-week follow up (T3), and at 1-, 3-, and 6-month follow ups (T4, T5, T6) for the analyses of peripheral blood and salivary biomarkers, including inflammatory mediators, neuroendocrine hormones, and microRNAs (see Multimedia Appendix 1).

Demographic information will include gender, age, ethnicity, marital status, military branch (ie, army, navy, or air force), and occupation. Psychological outcomes will be assessed through paper-based questionnaires administered during each contact with participants (Table 1). For further information on each outcome measure, refer to Multimedia Appendix 2.

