### Data Analysis

#### Objective 1: Effectiveness of 3MDR

The quantitative analysis strategy for this study will include a variety of descriptive, parametric, nonparametric, univariate, and multivariate approaches, as well as machine-learning techniques.

Descriptive statistics will be used to summarize demographic data of participants, including mean values, frequencies, and proportions.

Baseline between-group differences in sociodemographic, clinical, and neuropsychological variables will be assessed. For psychological outcomes, including self-reported PTSD symptom severity, anxiety and depression symptoms, and avoidance behavior, analyses will be conducted using mixed linear models. All of the analyses above will be carried out on an intent-to-treat basis. A two-tailed *P*<.05 will be considered statistically significant.

For preliminary assessment of the relation between treatment outcomes and relevant predicting

variables, exploratory regression analyses will be performed and a predicting variable will be considered to have potential predicting value in cases of *P*<.20. Predictors will then be combined in a regression model to determine which variables most strongly predict 3MDR treatment success. Missing data points, potentially due to missed visits or outcome measure abnormalities, will be handled with the last observation carried forward analysis of covariance [59].

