#### Objective 4: Machine Learning

In a supervised regression learning approach, the input of the machine-learning pipeline is considered to be the various types of data collected for each individual across every session. If the performance task is predicting reductions in symptom severity, then the output will contain psychological outcome measures. Such data will be divided into training and testing examples, whereby the statistical model will learn on the training set and then make data-driven predictions on the testing set to gauge how accurate those predictions were. During this process, the learner will optimize its predictions by comparing the predicted output with the observed output and then updating the parameters based on the severity of the errors made. Ultimately, the learned model will make individualized predictions about how a patient may respond to the treatment of 3MDR at a given time point.

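### Predictors for the week-9 outcome run up to the week-9 visit itself, diagnosis is a prediction target in a cohort where every patient has PTSD, and the exploratory P<.20 screen is refitted on the same patients

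*Protocol article*

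**What the plan says.** **Predictor window.** Study Timeline and Data Collection, Objective 4, sets the rule: "Physiological, biometric, biological, and qualitative data from T0 to T3 will be used to predict psychological outcome measures at week 9 plus follow-up sessions". Objective 1 of the same section gives the time points: "pre/post 3MDR sessions (T2.1-2.6), and at 1 week (T3), 1 month (T4), 3 months (T5), and 6 months (T6) postintervention". The text after Figure 3 places blood and saliva sampling at T3, among other times, and adds: "Qualitative interviews will occur at T3 through T6". The Subjective Measures paragraph says these interviews cover the effect of 3MDR on PTSD symptoms, and it dates the first one to week 10.

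**Diagnosis as a target.** Hypothesis 4 reads: "Machine-learning analysis will generate two accurate predictive models that may portend diagnosis, severity, and potential treatment outcomes". Specific Objectives and the Objective 4 data-collection text name diagnosis as well. Under Recruitment, eligible participants are those "who meet the Diagnostic and Statistical Manual-5 (DSM-5) criteria for a diagnosis of PTSD", with a CAPS-5 score of 30 or higher.

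**Screening.** Data Analysis, Objective 1: "exploratory regression analyses will be performed and a predicting variable will be considered to have potential predicting value" when P<.20. The retained predictors are then combined in one regression to find which most strongly predict treatment success.

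**Validation.** For machine learning, Data Analysis, Objective 4, says: "Such data will be divided into training and testing examples". For the biomarker partial least squares model, a leave-two-out, out-of-sample value is planned. No validation is attached to the P<.20 regression.

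**The concern.** A prediction model has to use information available before the outcome. If the inputs include material gathered at the outcome visit, and part of that material is the patient's own account of symptom change, the model partly reads off the outcome. A held-out test set does not cure this, because the test patients' inputs carry the same information.

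Hypothesis 4 claims accurate models, and the Discussion expects them to support decisions for individual patients. Inflated week-9 accuracy would feed straight into that claim. Inputs gathered after treatment also cannot inform a decision to start it.

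The diagnosis target has a different defect: a classifier needs both cases and non-cases. The P<.20 regression has a third: choosing predictors and estimating their joint fit on the same small sample makes noise look predictive.

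**Working it through.** **1. Is T3 the week-9 visit?**
- Table 1 columns: week 1 (baseline), week 3, weeks 4-8, week 9 (post).
- Six weekly sessions starting in week 3 fall in weeks 3, 4, 5, 6, 7 and 8.
- T3 is 1 week after the last session: 8 + 1 = week 9.

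This count is for the group treated first. It is an inference, because Figure 3 is not available.

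**2. What is collected at T3, against the week-9 outcome?**

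| Input type | When collected | Relation to week-9 outcome |
|---|---|---|
| Physiological, biometric, session audio/video | T2.1-T2.6 | before |
| Blood, saliva | several times, including T3 | T3 sample is concurrent |
| Interviews | from T3 (dated week 10 under Subjective Measures) | concurrent or later |

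For outcomes at 1, 3 and 6 months (T4, T5, T6), T3 data come first, so there is no timing problem there. The article gives nothing from which the size of the week-9 inflation could be computed.

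**3. Can diagnosis be modelled?** Planned patients: 20 + 20 = 40. All must meet DSM-5 criteria with CAPS-5 of at least 30, so entry diagnosis is constant: 40 cases, 0 non-cases. The 12 clinicians and operators complete questionnaires and interviews (Table 2). They are not described as giving biological or physiological data, so they cannot serve as non-cases. Table 1 does repeat CAPS-5 at week 9, 3 months and 6 months, so diagnostic status after treatment can vary.

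**4. What does the P<.20 screen do when nothing predicts?** The article gives no expected figure for these models and no number of candidates, so k = 10, 20 and 30 are assumptions. For k independent null predictors:
- expected number kept = 0.20 × k
- chance of keeping at least one = 1 − 0.80^k

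The fit was simulated with pure-noise predictors and outcome, 1,000 runs per cell. Each run screened at P<.20, refitted by least squares on the same people, and then scored the model on new data. Results at n=40:

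| k | Expected kept | Chance of at least one | Mean apparent R2 | Median new-data R2 | Any final term P<.05 |
|---|---|---|---|---|---|
| 10 | 2 | 0.893 | 0.17 | −0.17 | 42% |
| 20 | 4 | 0.988 | 0.27 | −0.27 | 53% |
| 30 | 6 | 0.999 | 0.38 | −0.35 | 64% |

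The last three columns are over runs that kept at least one predictor. With n=34 (the stated minimum of 17 per group), apparent R2 is 0.20 to 0.43. With n=20 (one group only), it is 0.31 to 0.60. New-data R2 is negative in every cell.

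**The case against.** Several points on the other side are fair.

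- **The timing problem is narrow.** Only blood, saliva and interviews reach T3, and psychological scores are not listed as predictors. Later outcomes are unaffected. Estimating current severity from concurrent biomarkers is a legitimate aim within the stated objective. This stands as a limit, but the rule still lists qualitative data to T3 as predictors of week-9 outcomes, and the interview asks about symptom impact.
- **The machine-learning aim is exploratory,** and the results are meant to inform a larger trial. This lowers the urgency, although Hypothesis 4 is stated as a formal hypothesis of accuracy.
- **Diagnosis can vary after treatment.** True, but the article never defines the target that way.
- **The P<.20 screen is labelled preliminary and exploratory and sits under Objective 1.** A reader might infer that it is part of the machine-learning pipeline and could by itself make Hypothesis 4 appear met. The text does not support that, and the point is confined to the Objective 1 regression.
- **Split unit.** A reader might infer that training and testing sets are divided by session record, so that one person appears in both. The article does not say so. It speaks of data collected for each individual and of sequential data, which fit a division by participant equally well, and the unit is a detail that an article may leave to fuller documents.
- **Safeguards exist.** A test set is planned for machine learning and leave-two-out validation for the biomarker model, so a claim that all the prediction work leaks and overfits would be too broad. Neither safeguard covers the P<.20 regression or corrects the predictor window.

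**Conclusion.** The point holds in three limited parts.

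1. For the week-9 outcome, the stated window admits data concurrent with or later than that outcome, so its accuracy would be overstated by an amount that cannot be computed from the article. This rests on reading T3 as week 9. The week-10 date for the interview does not rescue the rule; it places that predictor after the outcome. The two dates need reconciling.
2. Entry diagnosis is constant among the patients and cannot be a prediction target.
3. The Objective 1 screen-and-refit gives optimistic fit: at n=40 with 10 to 30 candidates, all null and independent (assumed), apparent R2 averages about 0.17 to 0.38 against a new-data R2 below 0.

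None of this touches the randomised comparison. It should be corrected before the models are fitted, because their reported accuracy depends on it.

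**What to change.** - **Window:** for week-9 outcomes, end predictors at the last in-treatment session (T2.6). Use T3 data only for the 1-, 3- and 6-month outcomes. For any model meant to inform the choice to start treatment, use T0/T1 data only. State one date for the T3 interview.
- **Diagnosis:** drop it as a target, or restate it as loss of diagnosis after treatment, for which CAPS-5 is already repeated.
- **Regression under Objective 1:** replace the P<.20 screen with penalised regression, or carry out the screening inside cross-validation folds, and report out-of-fold performance.
- **Clarification, not a correction:** add a phrase saying that training and testing sets are divided by participant.

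No new data collection is needed. The cost is changed wording, slightly more analysis work and lower reported accuracy.

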### Data Analysis

#### Objective 1: Effectiveness of 3MDR

The quantitative analysis strategy for this study will include a variety of descriptive, parametric, nonparametric, univariate, and multivariate approaches, as well as machine-learning techniques.

Descriptive statistics will be used to summarize demographic data of participants, including mean values, frequencies, and proportions.

Baseline between-group differences in sociodemographic, clinical, and neuropsychological variables will be assessed. For psychological outcomes, including self-reported PTSD symptom severity, anxiety and depression symptoms, and avoidance behavior, analyses will be conducted using mixed linear models. All of the analyses above will be carried out on an intent-to-treat basis. A two-tailed *P*<.05 will be considered statistically significant.

For preliminary assessment of the relation between treatment outcomes and relevant predicting

variables, exploratory regression analyses will be performed and a predicting variable will be considered to have potential predicting value in cases of *P*<.20. Predictors will then be combined in a regression model to determine which variables most strongly predict 3MDR treatment success. Missing data points, potentially due to missed visits or outcome measure abnormalities, will be handled with the last observation carried forward analysis of covariance [59].

A partial least squares (PLS) regression [60] will be used to identify combinations of blood biomarker concentrations that may distinguish the three treatment groups. PLS is a multivariate data reduction technique that creates orthogonal latent variables describing the maximal covariance between a set of predictors (biomarkers) and response (patient outcome) variables [61]. Between-group comparisons will be evaluated post hoc by generating bootstrapped mean differences of the group saliences for all group pairs, followed by the derivation of bootstrap ratios and empirical *P* values. In addition, model prediction performance will be quantitated by evaluating the prediction accuracy and posterior probability from separate PLS-discriminant analyses (PLSDA) on each group pair. PLSDA will also be used to evaluate the differences in biomarker profiles between groups. For both tasks, PLS and PLSDA, the weighted contribution of individual biomarker loadings will be quantitated by bootstrapped resampling (5000 iterations), followed by the generation of bootstrapped ratios and empirical *P* values. For evaluation of correlations between blood biomarkers and patient outcomes, an out-of-sample, leave-two-out cross-correlation (R2) value will be calculated on the PLS model. Random forest–based feature selection will be used to select the most relevant biomarkers that could be used to differentiate treatment groups. The random forest machine-learning algorithm is robust, with low bias and a reduced chance for overfitting.

For qualitative data analysis, audio recordings will be professionally transcribed and thematically analyzed in NVivo 12 software [62]. Thematic analysis involves examining text in detail to identify recurring patterns (“themes”) through both inductive and deductive reasoning [63]. Open codes will be combined into preliminary patterns that focus on similarities and differences within and between audio recordings to reduce the number of codes and provide more focus for the secondary level of coding [63]. Within the secondary level of coding, more abstract concepts will be assigned to broader categories of themes, and the relations between these concepts will be explored and verified through key quotes. Results will be distributed to a sample of the participants for member checking to assure the accuracy and trustworthiness of the research team’s interpretation of themes.

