### Sample Size

A sample size calculation was conducted using G*Power 3 [55], based on the primary hypothesis that 3MDR would result in significantly lower clinician-rated PTSD symptoms as compared to treatment as usual. To detect a significant interaction with at least a medium effect size, a minimal sample size of 17 participants was determined for each group. Because of an estimated 10% dropout and some attrition at measurements, the sample size was set at 20 participants in each group (Cohen f=1.0) using general linear modeling with one within-subjects factor (2 time points) and one between-subjects factor (2 interventions), and assuming a correlation of r=0.5 between the repeated measures, an α-level of .05, and a power (1 – β) of 0.8.

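### The only stated missing-data rule is last observation carried forward: its scope is unclear, and applied to the treatment comparison it would bias the 3MDR effect

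*Protocol article*

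**What the plan says.** All references are to the protocol article.

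- **Data Analysis, Objective 1, analysis model.** For psychological outcomes, "analyses will be conducted using mixed linear models". The examples listed are self-reported PTSD severity, anxiety, depression and avoidance; CAPS-5 is not named. The block ends: "All of the analyses above will be carried out on an intent-to-treat basis".
- **Same section, next paragraph.** After describing exploratory predictor regressions, it closes with the missing-data rule: "Missing data points, potentially due to missed visits or outcome measure abnormalities, will be handled with the last observation carried forward analysis of covariance". No other missing-data rule is given.
- **Sample Size.** The powered hypothesis is that "3MDR would result in significantly lower clinician-rated PTSD symptoms as compared to treatment as usual", with two time points, two groups and a correlation of 0.5. Seventeen per group becomes 20: "Because of an estimated 10% dropout and some attrition at measurements".
- **Table 1.** Up to week 9, CAPS-5 is taken at weeks 1 and 9 in both groups (and again later). PCL-5, GAD-7, PHQ-9, PABQ and the other self-report symptom scales are taken at week 3, weeks 4-8 and week 9 in the 3MDR group. In the control group they are first taken at week 9.

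**The concern.** LOCF assumes that a participant's score stays fixed after the last visit and then treats the filled value as observed. With CAPS-5 at weeks 1 and 9 only before crossover, a missing week 9 score becomes the baseline score, that is, no change at all. How far this distorts the contrast depends on how many are lost in each arm and how much each arm truly improves.

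A likelihood-based mixed model already uses every observed value and is valid under missing at random, so it needs no filling-in. LOCF with analysis of covariance is a single-endpoint analysis of filled values. The text does not say whether LOCF feeds the mixed model, replaces it for some outcomes, or applies only to the predictor regressions. With 20 per arm, a few dropouts matter, and an unclear rule leaves room to settle the method after the data are seen.

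**Working it through.** **Step 1: the planning effect.** Inputs from Sample Size: 2 groups, m = 2 time points, ρ = 0.5, α = 0.05, power 0.8. Medium is taken as f = 0.25 (convention; an assumption). With λ = f²·N·m/(1−ρ) and df 1 and N−2, N = 34 gives λ = 0.0625 × 34 × 2/0.5 = 8.5 and power 0.807. This reproduces 17 per group. (The printed f = 1.0 would need only N = 6; that is a separate matter.) The implied difference in change is √(4·f²·m/(1−ρ)) = √(4 × 0.0625 × 2/0.5) = 1.0 SD. The SD of change is √(2(1−ρ)) = 1 SD of the score.

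**Step 2: dropout.** The stated 10% is 4 of 40. Twenty against 17 per group allows 1 − 17/20 = 15%, or 6 of 40. The split by arm is not given, so it is varied.

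**Step 3: what LOCF estimates for CAPS-5 at week 9.** Let c be the control improvement, Δ the true effect, and d₁, d₀ the fractions lost on 3MDR and control. Those lost contribute zero change:

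LOCF difference = (1−d₁)(c+Δ) − (1−d₀)c

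If d₁ = d₀ = d, this is (1−d)Δ whatever c is. Otherwise c matters; 0.3 to 0.5 SD is assumed (0.5 in the 4/0 row).

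- 5 and 1 lost, c = 0.3: 0.75 × 1.3 − 0.95 × 0.3 = 0.69
- 5 and 1 lost, c = 0.5: 0.75 × 1.5 − 0.95 × 0.5 = 0.65
- 1 and 5 lost, Δ = 0: (0.95 − 0.75)c = 0.06 to 0.10

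**Step 4: simulation.** Baseline-adjusted ANCOVA, 20 per arm, missing completely at random, 2000 to 4000 trials per scenario. Ranges span the assumed c and separate runs.

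| Lost, 3MDR / control | True effect (SD) | Closed form (SD) | Simulated LOCF (SD) | Power, LOCF vs observed data | 95% CI coverage, LOCF |
|---|---|---|---|---|---|
| 2 / 2 | 1.0 | 0.90 | 0.90-0.91 | 87-89% vs 91% | 95% |
| 3 / 3 | 1.0 | 0.85 | 0.84-0.86 | 83-87% vs 89-91% | 94% |
| 4 / 0 | 1.0 | 0.70 | 0.71 | 65% vs 91% | 86% |
| 5 / 1 | 1.0 | 0.65-0.69 | 0.65-0.69 | 55-65% vs 88-89% | 81-84% |
| 1 / 5 | 0 | 0.06-0.10 | 0.06-0.11 | type I error 5.5-6.1% | not recorded |

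A further simulation (6000 runs per scenario) let dropout depend on baseline severity, with c = 0.5 and an average 20% lost in one arm only. LOCF gave 0.66 SD when the loss was on 3MDR and 1.14 SD when it was on control, for a true 1.0 SD. With no effect it gave a false difference of about 0.14 SD and a type I error of 0.081 to 0.085. ANCOVA on observed data stayed unbiased, at 0.048 to 0.052. With equal 10% loss and no effect, LOCF held its level (0.044).

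**Step 5: cost under the plan's own interaction test, equal loss.** LOCF keeps N = 40 but shrinks f to 0.25(1−d); observed data keep f = 0.25 but have N = 40(1−d).

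- 10% loss: power 0.79 (LOCF) vs 0.83 (observed)
- 15% loss: 0.75 vs 0.81
- 20% loss: 0.69 vs 0.78

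**Step 6: the self-report scales.** On Table 1, a 3MDR participant who leaves mid-course has a week 3 to week 8 score to carry to week 9. A control participant who misses week 9 has no earlier score. The same rule therefore imputes one arm and drops the other. No magnitude was computed for these scales.

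**The case against.** **Scope.** The intention-to-treat sentence closes the mixed-model block, and the LOCF sentence ends the following paragraph on predictor regressions. It may govern only those. A reader might infer that the plan fixes two incompatible methods for the same outcomes; the text does not establish that. What stands is that the wording ("Missing data points, potentially due to missed visits or outcome measure abnormalities") is general and is the only rule given, so the wider reading is likely but not certain.

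**Arms treated differently.** A reader might extend this to CAPS-5. Table 1 does not support it: both arms have weeks 1 and 9, so both carry baseline. The asymmetry concerns the self-report scales only. Even there, Recruitment gives the control group a baseline assessment, and Study Timeline and Data Collection describes collection from both groups at T0 and T1, so Table 1 may be incomplete.

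**Size.** A reader might take a loss of about a third of the effect as the expected result. The 5-to-1 split appears nowhere in the documents, and the article reports low dropout in both earlier 3MDR trials. At the stated 10% with equal loss, attenuation is about 10%, towards no effect, with coverage near 95%. Against this, allocation is unblinded and only one arm undergoes six trauma-exposure sessions before week 9, so unequal loss is plausible.

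**After week 9.** LOCF could carry a usual-treatment score into the control arm's 3MDR period. The powered comparison has two time points, however, and how control visits align with crossover is unclear, so nothing is built on this.

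**Conclusion.** The concern holds in limited form. The article states LOCF as its only missing-data rule without saying which analyses it covers. Applied to the week 9 CAPS-5 comparison, it dilutes the effect by the dropout fraction when loss is equal. When loss is unequal, it distorts the effect in a direction that cannot be known in advance. The modest case, 10% to 15% attenuation, rests on the protocol's own dropout figures. The larger distortions rest on assumed splits by arm and an assumed control improvement of 0.3 to 0.5 SD. The documents do not support saying that LOCF always favours 3MDR, nor that interval coverage fails at the stated dropout if loss is equal. Because this is a stated rule and not an omission, a later analysis plan would have to depart from the published text to correct it.

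**What to change.** 1. State which analyses the missing-data sentence covers, and remove LOCF from the treatment comparison.
2. Make the mixed linear model on all observed data the main analysis (valid under missing at random). Name CAPS-5 as an outcome in it, include baseline CAPS-5, and choose a covariance structure that 20 per arm can support.
3. Keep LOCF at most as a sensitivity analysis, beside one missing-not-at-random analysis such as a delta adjustment.
4. For the self-report scales, first reconcile Table 1 with the control group's baseline assessment in Recruitment and with the T0 and T1 collection in Study Timeline and Data Collection. If the control arm truly has no value before week 9, a baseline-adjusted model has no control baseline for these scales. Removing LOCF would then not recover control dropouts there.

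The cost is revised wording and modest extra programming, with no new data.
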